## Abstract

**Background:**

Cancer health disparities affecting low-income and minority patients are well documented. Root-causes are multifactorial, including diagnostic and treatment delays, social and financial barriers, and poor communication. Patient navigation and communication coaching (activation) are potential interventions to address disparities in cancer treatment. The purpose of this clinical trial is to test the effectiveness of an intervention combining patient navigation and activation to improve cancer treatment.

**Methods/Design:**

The Rochester Patient Navigation Research Program (PNRP) is a National Cancer Institute-sponsored, patient-level randomized trial (RCT) of patient navigation and activation, targeting newly-diagnosed breast and colorectal cancer patients in Rochester, NY. The goal of the program is to decrease cancer health disparities by addressing barriers to receipt of cancer care and promoting patient self-efficacy. The intervention uses trained, paraprofessional patient navigators recruited from the target community, and a detailed training and supervisory program. Recruited patients are randomly assigned to receive either usual care (except for baseline and follow-up questionnaires and interviews) or intervention. The intervention patients receive tailored assistance from their patient navigators, including phone calls, in-person meetings, and behind-the-scenes coordination of care. A total of 344 patients have been recruited. Outcomes measured at three month intervals include timeliness of care, patient adherence, patient satisfaction, quality of life, self-efficacy, health literacy, and cancer knowledge.

**Discussion:**

This unique intervention combining patient navigation and patient activation is designed to address the multifactorial problem of cancer health disparities. If successful, this study will affect the design and implementation of patient navigation programs.

**Trials Registration:**

clinicaltrials.gov identifier NCT00496678

## Background

Like the larger health care system in the United States (US), cancer care is fragmented, poorly coordinated and often not organized around the needs of the patient[1]. Many patients leave their health care visit confused about their diagnosis, prognosis, options for treatment, and next steps[2,3]. These problems are particularly severe for members of socially disadvantaged groups, including minority, low income, uninsured, non-English-speaking and low health literacy patients, and contribute to significantly higher cancer mortality rates[4].

Healthcare disparities based on social disadvantage, including race, ethnicity, socioeconomic status, language, and insurance, have been well documented for cancer screening[5], follow-up of abnormal cancer test results[6,7], and cancer treatment[7,8], [9]. The causes for disparities are multifactorial, including patient characteristics such as low health literacy, patient access barriers such as lack of healthcare insurance, provider factors such as cultural competency, and practice organizational factors such as a lack of systems to track patients at risk (Figure 1). In addition, interactions between factors may play an important role, particularly in the case of poor clinician-patient communication[10-12]. Studies in which equal treatment is meticulously provided to patients, irrespective of race, ethnicity, and socio-demographic backgrounds, have shown a significant reduction in disparities in treatment outcome for patients with breast and colorectal cancer,[13-15] indicating the potential to decrease cancer health disparities.

**Figure 1 F1:**
[figure not shown]
**Theoretical Model Linking Patient, Provider and Health System Factors to Cancer Health Disparities**[41]. (*indicates factor measured in the present study)

Two different models to address these problems have emerged in recent years: patient navigation (PN) and patient activation (PA) often referred to as "patient empowerment". We briefly review the history of each, discuss a conceptual framework for integration of the two into the same model, and conclude with our experience in implementing the integrated model in the setting of an ongoing randomized controlled trial.

### Conceptual Framework for Navigation-Activation

Because the causes of cancer health disparities are multi-factorial, an optimal intervention to address disparities must address different dimensions of the problem. The navigation-activation program combines PN and PA to improve patient-physician communication. These components are described briefly and the combined program is diagrammatically presented.

### Patient Navigation

For more than 40 years, community health workers (CHW's) have enhanced access to care among underserved populations in the United States (US)[16,17]. Freeman *et al *reported that 87% of inner-city patients with abnormal cancer findings who received PN from CHW's completed recommended biopsies compared to only 57% among those who were not navigated[18]. More recently, CHW's have been shown to improve outcomes in prenatal care[19], smoking cessation[20], child[21] and adult immunizations[22], and diabetes and depression management[23].

Patient navigation programs for cancer-related care have been developed across the US, including more than 100 PN programs sponsored by the American Cancer Society. Most PN programs share a number of common characteristics. Navigators assist patients with abnormal cancer screening or diagnostic tests by identifying and addressing barriers to quality and timely health care. For example, PN's may help patients keep track of appointments, interpret medical information, and provide social support[24].

### Patient Activation

Randomized controlled trials have demonstrated that interventions to train patients to assume more active involvement in their care and to ask more appropriate and relevant questions ("activation") can improve patients' outcomes[25,26]. Activation improves patient satisfaction with care and physician counseling[27,28], and adherence to treatment and follow-up appointments[29]. Pre-visit planning and coaching of breast cancer patients improves both patient and physician visit satisfaction[30]. Patient question-asking and provision of clear information by clinicians is associated with fewer diagnostic delays among black women with abnormal mammograms[12]. Patient assertiveness may attenuate racial and socioeconomic disparities in breast cancer evaluation[31]. These findings suggest that "activating" patients may be one means of improving cancer care for disadvantaged patients. However, not all such studies have positive results, and the specific techniques and settings of activation interventions are probably important to achieving desired results[32,28].

In prior studies, "activation" has been conceptualized as an intervention of limited duration, intended to provide education and empowerment. Conversely, PN has been structured as an ongoing, longer-term relationship between the patient and the navigator that provides a variety of supports. Navigation-activation brings activation together with PN as a longitudinal intervention. How can this intervention potentially decrease health disparities and improve health outcomes? Figure 1 provides a theoretical model to explain how this intervention may improve outcomes by affecting factors that mediate cancer health disparities. Disparities in care related to social disadvantage are mediated through *patient *access barriers, *provider *factors, and *practice *organizational factors. By potentially reducing delays in patient care and improving patient adherence and quality of care, patient navigation-activation seeks to improve quality of life, satisfaction, and survival.

### Cancer Health Communication

Effective communication between patients and healthcare providers is critically important for optimal care[33]. Poor communication may undermine patients' ability to understand their treatment options, cope with anxiety caused by cancer, make informed decisions regarding diagnostic and therapeutic procedures[34-36], and adhere to treatment[37].

The navigation-activation model is consistent with a recently-proposed conceptual framework for developing evidence-based interventions to improve health care communication[38,39]. A recent National Cancer Institute report on patient-centered communication suggests pathways by which effective communication is linked to high-quality medical decisions, adherence, patient and clinician satisfaction and improved health[38,40]. Navigators directly address *patient self-management*, one of the essential functions of communication. Through forming strong therapeutic relationships and providing both emotional and instrumental support, navigators assist patients in information exchange with providers, as well as other essential communication functions.

Navigators can help patients forge a more participatory dialogue with their clinicians. Specifically, navigators help patients ask clinicians questions that lead to a clearer understanding of their illness and treatment. They also coach patients to better inform clinicians about their experiences and preferences. Through this improved dialogue, patients come to posses both the information and support to participate effectively in decisions regarding their health.

## Methods/Design

### Study Design

The University of Rochester Patient Navigation Research Program (UR-PNRP) is a National Cancer Institute-funded, 5-year, randomized trial of PN for patients with a new diagnosis of breast or colorectal cancer, or with a positive screening test for these diseases[41]. The primary outcomes of the UR-PNRP are timeliness of care, guideline-concordant care, patient satisfaction, and quality of life.

### Selection of Study Sites

All oncology practices in the city of Rochester were recruited to participate in the PNRP program, as well as several primary care practices in Rochester, and several oncology practices in the surrounding community.

### Patient eligibility, recruitment, consent and randomization

Patients eligible for participation in the PNRP study are newly-diagnosed breast and colorectal cancer patients from participating practices, and patients with a positive screening test for these diseases. There are no exclusion criteria based upon socioeconomic status, race or insurance, but institutionalized patients and those with dementia or prior cancer (other than non-melanoma skin cancer) are excluded. Figure 2 is a flow chart of patient enrollment, randomization and progress through the trial. All study procedures have been approved by the Institutional Review Boards of the University of Rochester and participating sites in the area. All patients participating in the study provide written informed consent.

**Figure 2 F2:**
[figure not shown]
**Diagram of Patient Flow through the Clinical Trial**.

### Data Collection

Patient information is collected by research assistants prior to randomization. Patient demographic information is obtained from medical records and patient self-report, via in-person interview. Outcome measures are collected for both intervention and control patients at baseline and at three month intervals, as detailed in Table 1. In addition, information on barriers to care was collected by patient navigators, in the intervention group only, during semi-structured interviews with patients. A standardized form was used. Navigators also keep detailed records of their activities performed on behalf of their caseload of navigated patients, and the time each activity took.

**Table 1 T1:** Outcome and Other Measures of the Patient Navigation Research Program

Category	Title	Collection Times (mo)
**Primary Outcome Measures**		
Time to completion of Treatment	Time to completion of Treatment	
Satisfaction	Patient Satisfaction with Care	0;3;6;9;12
Cost	Cost	
		
**Knowledge/Health Literacy**		
Health literacy	Rapid Estimate of Adult Literacy in Medicine (REALM)	0
Knowledge	Breast Cancer Treatment Knowledge	0;3;FU
Knowledge	Colorectal Cancer Treatment Knowledge	0;3;FU
		

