#### Knowledge

We anticipate that navigation will be associated with improvements in knowledge. We will assess knowledge about breast cancer and colorectal cancer and its treatment using instruments developed by our investigators. It will be assessed at baseline for all subjects and at three months for primary care subjects and at six and twelve months for subjects with cancer.

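### Table 1 and the Knowledge section give different follow-up times for the knowledge tests; for cancer patients only baseline is certain to be common to both

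*Protocol article*

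**What the plan says.** The Data Collection section makes Table 1 the schedule: "Outcome measures are collected for both intervention and control patients at baseline and at three month intervals, as detailed in Table 1". The table's time column is headed in months ("Collection Times (mo"), and nothing in the table separates cancer patients from primary care subjects.

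Under Knowledge/Health Literacy, Table 1 lists "Breast Cancer Treatment Knowledge 0;3;FU" and "Colorectal Cancer Treatment Knowledge 0;3;FU". FU is not a month, and the article does not define it, either here or in the row for satisfaction with the navigator, where it appears again.

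The Knowledge section under Planned Analytic Approach does separate the groups: "It will be assessed at baseline for all subjects and at three months for primary care subjects", and then "at six and twelve months for subjects with cancer". It gives cancer patients no month 3 test.

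The abstract introduces its outcome list with "Outcomes measured at three month intervals include timeliness of care", and that list ends with cancer knowledge. Planned Analytic Approach names medical knowledge as a secondary outcome, and the Knowledge section expects navigation to improve it. The Data Analysis section compares continuous measures by two-sample t-tests. It states no time point and does not name knowledge among its examples.

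**The concern.** Two parts of one article give a collection rule for the same two instruments, and as printed the rules differ. The difference falls on cancer patients, who are now the main group: the Discussion explains that screening navigation was no longer needed and that recruitment moved to the cancer centers.

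What is at stake is whether knowledge data exist at the month where the arms will be compared. A knowledge questionnaire that was not given at a visit cannot be rebuilt from the chart. If the forms followed the text, cancer patients have no month 3 score. If they followed the table, month 6, month 12 or both may be missing, depending on what FU means. An unsettled schedule also leaves room to choose the comparison month after scores have been seen.

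**Working it through.** No sample size, power or alpha figure enters this point. The check compares two lists of months.

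**Inputs, cancer patients**

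- Table 1, breast and colorectal knowledge rows: {0, 3, FU}
- Knowledge section: {0, 6, 12}
- Knowledge section, primary care subjects, for reference: {0, 3}

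**Step 1: dated months only, leaving FU aside.** The months in both lists are {0, 3} ∩ {0, 6, 12} = {0}. Table only: {3}. Text only: {6, 12}. So 0 of the text's 2 follow-up months is printed in the table row, and the table's 1 dated follow-up month is not in the text's list for cancer patients.

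**Step 2: let FU vary.** The article does not define it, so I tried the plausible meanings.

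| Reading of Table 1 | Table's months for cancer patients | Shared with text | In text only | In table only |
|---|---|---|---|---|
| 3 for everyone, FU = month 6 | 0, 3, 6 | 0, 6 | 12 | 3 |
| 3 for everyone, FU = month 12 | 0, 3, 12 | 0, 12 | 6 | 3 |
| 3 for everyone, FU = one other visit | 0, 3, FU | 0 | 6, 12 | 3, FU |
| 3 for everyone, FU = months 6 and 12 | 0, 3, 6, 12 | 0, 6, 12 | none | 3 |
| 3 for primary care only, FU = months 6 and 12 | 0, 6, 12 | 0, 6, 12 | none | none |

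Only the last row gives full agreement, and it needs two unstated conventions at once. If FU is a single visit, it can match at most one of months 6 and 12. Across all rows, the only month always shared is 0.

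**Step 3: compare with the other questionnaires.** Table and text also differ for two other instruments, but in a milder way.

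- CASE: table 0, 3, 6, 9, 12; text for cancer patients 0, 3, 6, 12.
- FACT-B and FACT-C: table 0, 3, 6, 9, 12; text for cancer patients 0, 6, 12.

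In both, the text's months are a subset of the table's, so following the table still yields every month the text names. The knowledge rows do not give that assurance.

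**The case against.** The strongest reply is that Table 1 pools both subject groups, so that 3 belongs to primary care subjects and FU stands for the later visits of cancer patients. The two places would then agree. The satisfaction row fits this: its months 0, 3, 6, 9 and 12 are the union of what the Health care satisfaction section gives the two groups. But those same months are also exactly the cancer patients' schedule in that section, so the row cannot tell the two readings apart. The pooled reading is possible. It is stated nowhere, and Table 1 writes out 6, 9 and 12 in other rows where those months are meant.

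Some of the reply stands. That Table 1 assigns month 3 to cancer patients is an inference from the missing split by group. The references to three-month intervals do not prove it, because Table 1 itself departs from that interval for several measures. A reader might also infer that the two schedules share no follow-up at all; this holds for the printed months only, since FU could coincide with month 6, month 12 or both.

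It is also fair to say that the full protocol may define FU and that the analysis plan may name the comparison month. The absence of a named month from the article is therefore not the point. The point is that the article states the collection rule twice and the statements do not match.

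**Conclusion.** The point holds as an unresolved mismatch in the schedule for one secondary outcome. For cancer patients, baseline is the only knowledge assessment certain to be common to Table 1 and the Knowledge section, so data collected under one may not supply the follow-up months of the other. This rests on one assumption: that FU and the 3 do not carry the tacit meanings in the last row of the table above.

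A reader might infer more, and the documents do not support it:

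- No planned comparison is shown to have lost its data. The Knowledge section gives assessment times, not a six-month or twelve-month comparison.
- Nothing indicates that practices or forms used different schedules. The article describes collection by the study's research assistants.
- The number of patients affected cannot be given. The article reports 344 recruited, 178 of them assigned to navigation (so 344 − 178 = 166 to usual care), but does not split them into cancer and primary care subjects. The 200 and 300 cancer patients in Sample Size Determination are planning figures, not a count of missing assessments.
- The primary outcomes, randomization and power statements are untouched.

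The correction is worth making because it is cheap and because missed questionnaires cannot be recovered later.

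**What to change.** 1. State one knowledge-test schedule, by subject group, in both Table 1 and the Knowledge section, and replace FU with months. With 344 patients already recruited, the schedule should describe the forms actually collected. Adding visits on paper cannot recover past ones, so correct whichever place does not match the forms.
2. Before arms are compared, name one follow-up month for cancer patients from that schedule. If the analysis plan already names one, check that it is a month at which the test was given.
3. Compare arms at that month by a regression of the follow-up score on arm and baseline score, instead of an unadjusted two-sample t-test. Both schedules include the baseline score, so no new data are needed. If the baseline and follow-up scores correlate at r, the residual variance falls by a factor of about 1 − r². The article gives no value for r, so I claim no specific gain.

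The cost is wording in two places and minor analysis work.

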**Quality of Life**		
Quality of Life	Impact of Events Scale (IES)	0;3;6;9;12
Cancer Related Health Status	Functional Assessment of Cancer Therapy-Breast Cancer (FACT-B)	0;3;6;9;12
Cancer Related Health Status	Functional Assessment of Cancer Therapy-Colorectal Cancer (FACT-C)	0;3;6;9;12
		
**Medical Conditions**	Charlson Commorbidity	chart review
		
**Adherence**		
Adherence	Medical Outcomes Study (MOS) General Adherence Items	0;3;6;9;12
Beliefs	Beliefs about Medication Questionnaire (BMQ)	0;3;6;9;12
		
**Interaction**		
Attachment Style	Relationship Questionnaire (Attachment Style)	0
Intensity	Navigator Perceived Time and Emotional Intensity of Patient Navigation	0;3;6;9;12
Self Efficacy	The Communication and Attitudinal Self-Efficacy Scale (CASE)	0;3;6;9;12
Satisfaction	Patient Satisfaction with Navigator	3; FU
Tracking	Patient Navigator Tracking Logs - encounter times, barriers, and actions	Throughout

### Recruiting and Training Patient Navigators

Non-medically-trained persons from the community were recruited to be PN's. Minimal selection criteria included a high school degree[42], reliable mode of transportation and a current driver's license. Preference was given to applicants with experience in case management. Desirable personal qualities included strong interpersonal and communication skills, fluency in Spanish and English, ability to learn, dependability, initiative, and passion and commitment to improving health care for underserved patients.

### The Navigator Curriculum

The first navigators received a six-month, intensive training program that covered the basics of cancer diagnosis and treatment and each of the PN tasks, as outlined in Table 2. Subsequently, the training has been shortened to less than half this time. All navigators also completed an 80-hour core curriculum (The Cornell Project) developed by New York State for the training of CHW's and yearly two to three day national training seminars, sponsored by the American Cancer Society. Project investigators, other medical professionals, local government resources, and local private agencies were recruited to participate in the training program. Training in patient activation involves a series of observed and evaluated interactions with trained, standardized cancer patients (actors trained to portray patients). A navigator manual was created, including standard operating procedures, lists of community resources and patient educational materials, as well as materials to reinforce the training curriculum.

**Table 2 T2:** Navigator Training Program

Training Activity	Concepts	Educator(s)
**In-House Training**		

Cancer Health Disparities Overview	Patient, provider, practice and health system barriers to care	Program director
Research 101	Human subject protection, HIPAA^a^	Project coordinator
Standard Operating Procedures and Case Management		Project coordinator, PN supervisor
Orientation to Participating Health Care Settings	Visit practices; computer medical database training	Project coordinator, PN supervisor
Cancer 101	Physicians teach PN's basics of cancer diagnosis and treatment; shadowing MD's at patient office visits, colonoscopies; observing tumor board conference at cancer center; visit to pathology laboratory	Medical oncologist, surgical oncologist
Interpersonal Communication 101	"How to talk to your doctor", "Patient empowerment", others	PN Supervisor; communications researcher; staff of non-profit agency
Computer Literacy	Email; Microsoft office; computerized calendars; internet searches for resources and patient care guidelines	Project coordinator, research assistants
Domestic Violence	Child protective services and domestic violence lectures	Department of Health and Human Services
Community Resources	Transportation, financial counseling, interpreter services, child care, social work	Social worker from cancer center
Motivational Interviewing	Self-determination and empowerment	Research assistant
End of Life Care	Transition from treatment to palliation	Hospice nurse
Personal Safety	Actions to minimize risk	Police department
The Health System	Review of government and private health insurances	PN supervisor
The Initial Assessment Interview	A semi-structured interview was designed, and PN's learned to conduct it, using the skills of "joining", history-taking, assessment of patient barriers, and making follow-up plans	PN supervisor

